## Background

Stroke is, worldwide, the first cause of disability in adult-older individuals, and the second cause of death and dementia (Leys et al., 2005). Annually, ~16 million of first ever strokes occur in the world, causing 6.3 million deaths (Katan and Luft, 2018; Barbay et al., 2018). Stroke is costly: total cost in Europe is estimated at about €60 billion/year, of which 45% incurred by healthcare systems, 27% for informal care costs, and 22% for loss of productivity (Katan and Luft, 2018; Barbay et al., 2018; Luengo-Fernandez et al., 2020). Future projections suggest an increase in stroke cases, primarily due to the rise in life expectancy (Luengo-Fernandez et al., 2020).

Post-stroke cognitive impairment (PSCI) encompasses all forms of mild to severe cognitive impairment when onset is temporally associated with stroke (El Husseini et al., 2023). The cognitive profile of PSCI is heterogeneous and depends on the type, location, and severity of cerebrovascular lesions. Cognitive hallmarks of stroke-related cognitive impairment include aphasia, neglect, apraxia, and agnosia, and a disconnection syndrome caused by the dysfunction of integrated brain networks and characterized by deficits in information processing speed and executive functions (Shin et al., 2024). Epidemiological data report that ~75% of stroke survivors experience cognitive changes in the acute phase, 47% if we exclude patients with pre-dementia (El Husseini et al., 2023). At a medium-long term cognitive impairment persists in ~50% of patients, a majority fulfilling criteria for mild cognitive disorder (D'Souza et al., 2021). These latter could maximally benefit from cognitive treatment options especially because there are no drug treatments available as today. Cognitive problems after stroke are associated with poor outcomes in terms of recurrence of major vascular events, disability, institutionalization, and death.

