**Figure 1 F1:**
[figure not shown]
CIPS-TER study experimental design.

The study is carried out at the Stroke Unit of Careggi University Hospital and at General Rehabilitation Unit of IRCCS Don Carlo Gnocchi in Florence, in accordance with the Helsinki Declaration. The study was approved by Local Ethics Committee (25546_spe) and each patient gave a written informed consent.

Patients included in the study were diagnosed with either ischemic or hemorrhagic stroke, regardless of lesion site. Neuroimaging was used to confirm diagnosis.

The study aims at estimating the incidence of post-stroke cognitive impairment in the short and mid-term, and at investigating the efficacy of a CTR program in reducing the risk of CI 6 months after stroke, the generalizability of cognitive training to real life and the impact on cognitive performances. It also aims at evaluating the effect of cognitive training on real-life activities (independence in daily living and quality of life). In the treated group, feasibility, adherence and appreciation of the CTR will also be evaluated.

Inclusion criteria of the study are: ischemic or hemorrhagic stroke (within 5–21 days after onset); age >18 years; evidence of impairment in global cognitive efficiency; NIHSS motor arm item = 0 in at least one arm; fluid Italian speaking; ability and willingness to sign informed consent.

Exclusion criteria are: normal cognitive functioning; pre-existing dementia; severe aphasia; motor deficits in both upper limbs; visual deficits.

All participants diagnosed with ischemic/hemorrhagic stroke are assessed within 5–21 days from onset. Table 1 shows the type of information collected and the instruments applied. Clinical information is retrieved from the clinical records; instruments are administered to patients and caregivers.

**Table 1 T1:** Data collected for screening and baseline evaluation and types of instruments used.

**Study phase**		**Data collection and instruments**
Screening Evaluation	Stroke severity	• NIHSS^*^
	Global cognitive efficiency	• Montreal cognitive assessment (MoCA)^*^ (Nasreddine et al., 2005)
	Verbal comprehension ability	• Token Test in those patients with 1 or 2 at NIHSS language item^*^ (Renzi and Faglioni, 1975)
	Pre-existing cognitive impairment	• Informant questionnaire on cognitive decline in the elderly (IQ-Code)^#^ (Jorm, 2004; van Nieuwkerk et al., 2021)

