# Caregiver interview.

For each patient, a caregiver or informant is identified and interviewed to assess the premorbid status. Cognitive premorbid status is evaluated by means of the informant questionnaire on cognitive decline in the elderly (IQ-Code) short form (16 items). IQ-Code explores the changes in daily activities requiring memory and other cognitive abilities observed over the last 10 years. An excellent accuracy of the IQ-CODE for detecting pre-existing dementia in transient ischemic attack and stroke was recently found for an optimal cut-off of >3.48 in a large longitudinal population-based study (Jorm, 2004; van Nieuwkerk et al., 2021). To assess severity of aphasia, we use the language item of the NIHSS according to the following criteria: if the score is 3, the patient is excluded. If the score is 1 or 2, we assess reading capabilities and comprehension. For this latter, we use the Token test (Renzi and Faglioni, 1975), excluding patients with an adjusted score below the 5th centile of the normal population. To be included, patients need to be able to use the tablet autonomously. For this purpose, we exclude patients with severe visual and hearing deficits and those not able to move at least one arm (motor item = 0 in at least 1 arm, not necessarily the dominant one).

Cognitive performances at this stage are assessed by means of Montreal Cognitive Assessment (MoCA). MoCA is a 30-point test recommended by the harmonization standards for the diagnosis and assessment of patients with vascular cognitive impairment, and it covers eight cognitive domains: verbal memory, visuospatial abilities, executive functions, attention, concentration, working memory, language, and orientation to time and place (Nasreddine et al., 2005). The predictive value of MoCA in the acute phase of stroke on the diagnosis of mid-term cognitive impairment is the topic of a previous publication from the proponents (Salvadori et al., 2013). MoCA is a good predictor of mid-term PSCI, independent of other clinical, neurological, and functional characteristics, and a cut-off of 21 is found to have good sensitivity (91%), specificity (76%), positive predictive value (80%), and negative predictive value (89%).

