To evaluate cognitive performance, raw scores have been demographically adjusted and converted into an ordinal Five-point scale (equivalent score, ES) using national normative data. Equivalent score is a non-parametric norming method based on percentiles distributions, and scores range varies from 0 to 4: ES = 0 corresponds to an impaired performance (i.e., adjusted score below the outer confidence limit for the 5th centile of the normal population); ES = 1 corresponds to a borderline performance (i.e., adjusted score between the outer and inner confidence limits for the 5th centile of the normal population); and ES = 2–4 represents a normal performance (i.e., adjusted score above the inner confidence limit for the 5th centile of the normal population). When ES methodology is not available, performance was classified according to the reference cut-off, as “normal” when the adjusted score was above the 5th percentile or “abnormal” when the adjusted score was below the 5th percentile in the normal population.

To be included in the study, patients must score ≤ 21 on total MoCA adjusted score (Salvadori et al., 2013) or fail in at least one cognitive domain of MoCA. We consider the inclusion of patients with ES ≤ 1 in at least one cognitive domain according to Aiello et al. (2022).

Through the patient's clinical record, the following information is collected: demographics, medical history, comorbidities, vascular risk factors, home therapy, index stroke clinical and instrumental characteristics (Wardlaw et al., 2013; Duering et al., 2023; Scheltens et al., 1992). A centralized reading of available neuroradiological examinations, such as CT and MRI brain, is performed by an expert vascular neurologist/neuroradiologist.

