At baseline, patients undergo a cognitive and mood assessment to investigate: neglect (star cancellation test; Halligan and Robertson, 2000; Wilson et al., 1987), apraxia (ideomotor apraxia test; Spinnler and Tognoni, 1987), fragility [Tilburg Frailty Indicator—TFI (Gobbens and Uchmanowicz, 2021; Mulasso et al., 2016) and Fried criteria (Fried et al., 2001) with IPAQ (Mannocci et al., 2010)] and cognitive reserve (CRI Questionnaire; Nucci et al., 2012). At 7 days after discharge, a telephone interview is conducted to investigate: functional state (ADL, IADL, and mRS; Katz et al., 1963; Lawton and Brody, 1969), quality of life [Stroke adapted sickness impact profile—SA-SIP (Buck et al., 2000) and EuroQol (Dorman et al., 1998)] and mood (CES-D; Lau et al., 2023).

During hospitalization, the caregiver interview involves the investigation of the patient's premorbid functional state (ADL and IADL; Katz et al., 1963; Lawton and Brody, 1969) and the possible presence of cognitive decline before stroke (IQ-Code; Jorm, 2004; van Nieuwkerk et al., 2021).

Stratified block randomization is used to assign participants to the experimental (tele-rehabilitation) or control group (standard care). This method ensures an even distribution of participants across predefined strata and minimizes imbalance in group sizes over time. Participants are stratified based on age, sex, NIHSS and MoCA scores. These variables were selected due to their potential influence on the study outcomes. Blocks of fixed size were generated to ensure that the number of participants in each group remained balanced throughout the enrollment process.

Randomization sequences were created using a computer-based random allocation software by the researchers of the Institute of Neuroscience (Florence) of the Italian National Research Council, who were not involved in participant recruitment or data collection and were in charge of the centralized randomization procedure. To prevent selection bias, randomization sequences are concealed from field workers.

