Experimental group: the cognitive telerehabilitation program is based on a medical device, with EU declaration of conformity. The product includes a central workstation, located in the clinic. From the central workstation, an expert psychologist ([name]), follows patients' performances and weekly adapts the difficulty of the tasks according to patients' performances. During the 2-month treatment, patients' compliance to the training sessions will be recorded.

Each patient randomized in the experimental group receives a tablet for the telerehabilitation program. This foresees sessions of telerehabilitation for 60 min per day, for 5 days a week, for a total of 8 weeks (totally making 40 h of individual treatment). Exercises are meant to work on the main cognitive domains: memory, language, attention, executive functions, visual-spatial and praxis skills. The daily treatment session includes 10-min exercises for each of the six cognitive domains.

Control group (standard care): participants are instructed to have a normal lifestyle and receive conventional treatments based on clinical indications provided by their referring physicians.

Two months after enrollment, at the end of the treatment session, a phone interview will be conducted to investigate satisfaction and gratification regarding CTR.

The endpoints of the study are to detect cognitive deficits in acute post-stroke phase and measure the impact these deficits might have on functional autonomy and quality of life of patients 6 months after stroke. The primary outcome will be the diagnosis of cognitive impairment, including mild cognitive impairment (MCI) and dementia according to the DSM-5 criteria for the diagnosis of mild or major neurocognitive disorders, respectively (American Psychiatric Association, 2022). Secondary endpoints will include assessment of functional status in daily life, quality of life, frailty and cognitive efficiency.

As shown in Table 2, the 6-month follow-up includes a neurological assessment with updates of clinical information, neurological exam and functional evaluation (NIHSS and mRS). Cognitive performances will be assessed by means of a comprehensive multidomain neuropsychological battery. The medical doctor and the neuropsychologist who will perform the follow-up visit will be blinded to treatment group.

**Table 2 T2:** Data collected for the 6-month follow-up visit with types of instruments used.

**Cognitive domain**	**Test**

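### Mild pre-stroke decline does not bar entry and is not separated from post-stroke impairment in the stated primary analysis, although the IQ-CODE needed to separate it is already collected

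*Protocol article*

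**What the plan says.** **Pre-stroke status.** The Methods state: "Exclusion criteria are: normal cognitive functioning; pre-existing dementia; severe aphasia". Decline short of dementia is not on the list. The instrument is the 16-item IQ-CODE, and the one cut-off quoted is a dementia cut-off: its accuracy "for detecting pre-existing dementia in transient ischemic attack and stroke was recently found for an optimal cut-off of >3.48". The caregiver interview is also said to cover "the possible presence of cognitive decline before stroke", so milder decline is recorded.

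**Entry after the stroke.** The Methods require that "patients must score ≤ 21 on total MoCA adjusted score" or, alternatively, that they fail at least one MoCA domain. Both are judged on a MoCA taken after the stroke.

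**Primary event.** "The primary outcome will be the diagnosis of cognitive impairment, including mild cognitive impairment (MCI) and dementia according to the DSM-5 criteria". Nothing in the article requires the disorder to be new, or worse than the pre-stroke state.

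**Primary analysis.** Statistical analysis, objective 1, compares proportions by a chi-square test and frames the aim as lowering the incidence of impairment that persists at 6 months. Randomization is stratified by age, sex, NIHSS and MoCA. The covariates listed under objective 3 do not name the IQ-CODE.

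**Background.** Post-stroke cognitive impairment is described there as a condition that "encompasses all forms of mild to severe cognitive impairment when onset is temporally associated with stroke".

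**The concern.** A patient who was mildly impaired before the stroke can pass the dementia exclusion and meet the MoCA rule. At 6 months that patient may have recovered everything the stroke took away and still meet the criteria for a mild disorder. The primary outcome records an event, although by the Background's description this impairment did not begin with the stroke.

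Two things are at stake. The first is interpretation: the primary result mixes impairment that followed the stroke with impairment that preceded it, and the stated analyses cannot tell them apart. The second is sensitivity: if these patients avoid the event less readily than others, they add events to both arms and pull the difference toward zero. The Discussion already concedes that the modest sample may limit power.

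**Working it through.** **1. The plan's own figure.** Statistical analysis gives 100 patients (50 per arm), two-sided alpha 0.05 and 80% power, without a control risk or an effect, so the figure cannot be reproduced. Solving backwards with the pooled-variance two-proportion formula, 50 per arm gives 80% power for 50% versus 23.3%, a difference of 26.7 points. This shows only the scale of effect the trial can detect.

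**2. Model.** Let *f* be the share of enrolled patients with mild pre-stroke decline. Suppose they all have the event under standard care, and a fraction *q* of those treated avoid it. The other patients have risks of 50% (control) and 25% (treated).

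- Control risk = *f* + (1 − *f*) × 0.50
- Treated risk = *f*(1 − *q*) + (1 − *f*) × 0.25
- Difference = (1 − *f*) × 0.25 + *f* × *q*

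The Background gives about 50% for medium- to long-term impairment in stroke patients generally; using it for patients without prior decline is an assumption. The 25%, *f* and *q* are all assumed.

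**3. Results.** Exact power of the uncorrected chi-square test, 50 per arm:

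| *f* | *q* | Control | Treated | Difference (points) | Power |
|---|---|---|---|---|---|
| 0% | – | 50% | 25% | 25 | 75% |
| 10% | 0 | 55% | 32.5% | 22.5 | 64% |
| 20% | 0 | 60% | 40% | 20 | 54% |
| 30% | 0 | 65% | 47.5% | 17.5 | 44% |
| 20% | 10% | 60% | 38% | 22 | 62% |
| 20% | 25% | 60% | 35% | 25 | 73% |
| 20% | 50% | 60% | 30% | 30 | 88% |

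The formula shows when dilution occurs: the difference falls below 25 points only if *q* is below 25%, that is, if these patients gain less in absolute terms than the others.

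**4. Placing the 50% differently.** Suppose 50% is the control risk of the whole sample, including these patients, and treatment halves the risk only in the rest. At *f* = 20% the treated risk is 0.20 + (0.50 − 0.20) × 0.5 = 35%, the difference is 15 points and power is 34%.

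**5. What separation could recover.** If the patients with prior decline could be identified perfectly and set aside, 45, 40 or 35 per arm would remain at *f* = 10%, 20% or 30%. At 50% versus 25%, power is 70%, 65% or 59%, against 64%, 54% or 44% for all patients when *q* = 0. An imperfect IQ-CODE recovers less. At *f* = 20% and *q* = 25%, restriction would lower power, from 73% to 65%. Restriction therefore suits a supportive analysis, not the primary one.

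**The case against.** **The Background sentence is not the endpoint definition.** It describes the condition from the literature. The efficacy aim is a lower risk of cognitive impairment at 6 months, every enrolled patient is impaired at entry, and the endpoint measures whether impairment is still present. This stands in part: there is no flat contradiction. But the article also speaks of the incidence of post-stroke impairment and of persistent impairment, and the stated analyses cannot separate either from impairment that was there before.

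**Covariates and supportive analyses belong in the analysis plan.** Fair, and an unseen plan may already contain them. For that reason the point is a cheap improvement to a stated analysis, not an error in the article.

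**Patients with prior decline are not lost causes.** A reader might infer that they are unavoidable failures who will have the event whatever the training does. No text in the article shows this. Some may test above the threshold for a mild disorder after training, and at *q* = 25% the loss in the illustration all but disappears.

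**Randomization handles it.** It spreads these patients over both arms, so no bias is expected. A reader might infer a biased comparison; the documents do not support that. Chance imbalance remains possible because the IQ-CODE is not a stratification factor.

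**Breadth is intended, and vulnerability is modelled.** The Discussion wants a wide range of deficits, and objective 3 lists baseline cognition, frailty and pre-existing brain changes. Neither conflicts with the proposal, which excludes nobody. The objective 3 models look for predictors of efficacy and are not an adjusted primary comparison.

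**Conclusion.** The point holds as an inexpensive improvement. Only pre-stroke dementia is excluded, any mild or major disorder at 6 months counts as an event, and the stated test makes no use of the pre-stroke measure that is collected. Patients with milder prior decline can therefore enter and may count as events after returning to their pre-stroke state.

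The size of any dilution cannot be fixed from the article. At an assumed 20% share, the scenarios above run from 34% to 88% power, depending on how these patients respond and where the 50% risk is placed, against 75% with none of them. Even the direction of the power change depends on their response. What does not depend on these assumptions is that the primary comparison, as stated, cannot show how many of its events preceded the stroke.

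**What to change.** Keep eligibility and the primary event unchanged, and add three items to the analysis wording:

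1. An adjusted analysis of the 6-month diagnosis with the screening IQ-CODE score as a covariate.
2. A supportive analysis of the primary outcome in patients without pre-stroke decline on the IQ-CODE, with the threshold fixed before unblinding. The quoted >3.48 is a dementia cut-off, so a separate threshold for milder decline has to be chosen and justified.
3. A report, by arm, of how many primary events occurred in patients with pre-stroke decline.

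The score is already collected, so no visit, instrument or patient is added. The cost is one more covariate and a smaller sample in the supportive analysis. The gain in power is modest at best, so the case rests on interpretability.

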### Statistical analysis

The sample size was determined a priori based on data reported in previous studies and reviews on cognitive rehabilitation, along with feasibility and logistical considerations. These included the actual flow of stroke patients admitted to Careggi University Hospital and the Intensive Rehabilitation Unit of IRCCS Don Gnocchi during the planned 12-month enrollment period, along with the availability of dedicated spaces, appropriate settings, and personnel.

Yearly, ~400 stroke patients are admitted to the Stroke Unit of Careggi University Hospital, and ~130 patients are referred to the Intensive Rehabilitation Unit of IRCCS Don Gnocchi. Based on an estimated screening pool of ~550 patients during an enrolment period of 12 months, and accounting for an expected frequency of cognitive deficits in 75% of stroke patients during acute phase (enrolment period), as well as a substantial proportion of ineligible patients and refusals, we estimate to enroll ~100 patients. Eligible patients will be randomized in a 1:1 ratio: 50 will be allocated to the experimental group receiving the telerehabilitation program and 50 to the control group receiving standard care. Both groups will be balanced for key demographic and clinical characteristics. This sample size was determined based on pilot studies and a power analysis to ensure a statistical power of 80% to detect significant differences between the two groups assuming a two-sided alpha level of 0.05.

The data management system will include automatized procedures of data analysis. Specifically, independent sample *t*-tests and chi square tests will be used to compare demographics, vascular risk factors, and global cognitive and functional status, and the results will be available in real time during the whole enrollment period. Stratified block randomization will be employed to balance potential prognostic factors—such as age, gender, MoCA scores, and NIHSS scores—across the two groups, minimizing confounding and enhancing internal validity.

At the conclusion of the 6-month follow-up, primary and secondary outcome analyses will be conducted using SPSS version 28. The analysis will focus on three main objectives:

1) Effectiveness in Reducing Persistent Cognitive Impairment: The efficacy of the telerehabilitation program in reducing the incidence of persistent cognitive impairment at 6 months will be assessed using a chi-square test to compare proportions between groups.2) Impact on Daily Life Abilities: The effectiveness of the telerehabilitation program in improving patients' functional outcomes will be evaluated through within-group (pre-post) and between-group comparisons. Dependent variables will include functional independence measures, quality-of-life scores, changes in frailty status, and cognitive performance metrics.3) Predictors of Effectiveness of the telerehabilitation program: Multivariate regression models will be used to identify predictors of telerehabilitation efficacy. Covariates will include demographics (age, sex), cognitive resilience, baseline cognitive and functional abilities, TFI score, index stroke severity, and pre-existing brain structural changes.

The enrolment activities began in April 2024 and are ongoing. Since then, consecutive patients admitted with a diagnosis of ischemic or hemorrhagic stroke are being evaluated for participation in the study.

The flow-chart of the study is shown in Figure 2.

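### The primary chi-square ignores the four factors that stratify randomisation: it stays valid, but it is conservative and loses power to the extent that those factors are prognostic

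*Protocol article*

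**What the plan says.** The randomisation paragraph in Methods states: "Participants are stratified based on age, sex, NIHSS and MoCA scores". It gives the reason: "These variables were selected due to their potential influence on the study outcomes". It adds "Blocks of fixed size were generated", without giving the block size or any cut-point for the strata. The Statistical analysis section repeats the aim: "Stratified block randomization will be employed to balance potential prognostic factors".

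Objective 1 of the same section then fixes the primary comparison: "persistent cognitive impairment at 6 months will be assessed using a chi-square test to compare proportions between groups". No stratification or covariate enters it. The only regression is in objective 3, which looks for predictors of telerehabilitation efficacy and is not the test of the primary treatment effect.

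Two statements on MoCA bear on the size. Methods cites an earlier study in which a cut-off of 21 predicted mid-term impairment with sensitivity 91%, specificity 76%, positive predictive value 80% and negative predictive value 89%. For entry, "patients must score ≤ 21 on total MoCA adjusted score", or else must fail at least one MoCA domain. Patients on both sides of 21 can therefore be enrolled.

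**The concern.** When a prognostic factor is balanced between arms by design, it no longer adds to the chance variation of the difference in proportions. The chi-square variance is built from the pooled proportion and still counts that variation. The test statistic is then too small on average, the true type I error falls below 5%, and power falls with it.

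At stake is efficiency on the only primary test of a 100-patient trial. The article itself concedes in its Discussion that the modest sample may reduce power. A null result could in part reflect the choice of test.

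**Working it through.** **1. The plan's own figure.** The article claims 80% power with 50 per arm, "assuming a two-sided alpha level of 0.05", but gives no control rate and no effect, so the sample size cannot be reproduced. What 50 per arm can detect follows from the usual formula, n = [1.96·√(2p̄q̄) + 0.8416·√(p₁q₁ + p₂q₂)]² / (p₁ − p₂)². With p₁ = 0.50 (the background figure for persisting impairment) and p₂ = 0.233, p̄ = 0.3665 and n = (1.3356 + 0.5511)² / 0.267² = 3.560 / 0.0713 = 49.9. The detectable drop is about 27 points, which leaves little power to spare.

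**2. How prognostic is MoCA?** The four cited figures agree with one another at a prevalence of 0.513:
- PPV = 0.91×0.513 / (0.91×0.513 + 0.24×0.487) = 0.80
- NPV = 0.76×0.487 / (0.76×0.487 + 0.09×0.513) = 0.89
- Odds ratio = (0.91/0.09) × (0.76/0.24) = 32

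In that earlier study the risks were thus about 80% at or below the cut-off and 11% above it.

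**3. Why the test is conservative.** Let s be the share of patients at or below 21, with risks r₁ (at or below) and r₂ (above), and overall risk p. Under exact balance the variance ratio is V = [s·r₁(1−r₁) + (1−s)·r₂(1−r₂)] / [p(1−p)], and the chi-square's true level is 2·[1 − Φ(1.96/√V)]. With s = 0.5 and r₁ = 0.80:
- r₂ = 0.11: V = 0.1290/0.2480 = 0.520, level 0.7%
- r₂ = 0.30: V = 0.1850/0.2475 = 0.747, level 2.3%
- r₂ = 0.45: V = 0.2038/0.2344 = 0.869, level 3.6%

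**4. Simulation with realistic, imperfect balance.** Assumptions: 100 patients; four binary factors, so 16 strata; permuted blocks of 4; MoCA cut at 21; only MoCA prognostic; control risk 80% at or below 21; common odds ratio 0.3 (80% becomes 54.5%); 10,000 trials per row. The Pearson chi-square is compared with a Mantel-Haenszel (MH) test on the two MoCA strata.

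| Risk above 21 | Share ≤21 | Type I error, chi-square / MH | Power, chi-square / MH | Loss (points) |
|---|---|---|---|---|
| 11% | 50% | 1.3% / 5.1% | 38.4% / 58.9% | 20.5 |
| 11% | 70% | 1.8% / 5.1% | 55.1% / 68.4% | 13.3 |
| 11% | 90% | 4.2% / 5.1% | 70.5% / 75.5% | 5.0 |
| 30% | 50% | 3.2% / 5.0% | 63.4% / 72.5% | 9.1 |
| 30% | 70% | 3.1% / 5.2% | 68.5% / 74.6% | 6.1 |
| 30% | 90% | 4.4% / 4.9% | 75.2% / 77.7% | 2.5 |
| 45% | 50% | 3.8% / 4.8% | 76.2% / 79.0% | 2.8 |
| 45% | 70% | 4.0% / 4.9% | 75.6% / 77.9% | 2.3 |
| 45% | 90% | 4.5% / 4.5% | 77.6% / 78.6% | 1.0 |

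Repeat runs move single cells by about a point. Across runs, chi-square type I error reaches 4.8%, the loss in the third row lies between 4 and 6 points, and the smallest losses at 30% to 45% risk are about 0.

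**5. Other patterns.** These runs used 4,000 trials each.
- If all four factors carry the same odds ratio of 1.5, 2, 3 or 4 and the control rate is 50%, chi-square type I error is 4.7%, 4.8%, 3.9% or 2.7%. Power for a 27-point drop, chi-square against adjusted logistic, is 82/85, 83/86, 84/90 or 85/92%.
- At odds ratio 3 without stratified allocation, chi-square type I error is 5.6%. The conservatism therefore comes from stratifying and then not using the strata.
- With weak MoCA prognosis (60% against 35%, 60% of patients at or below 21), the 16-stratum MH test gains nothing: 83% against 83% power for a 27-point drop.

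**The case against.** The strongest reply is that nothing here threatens the conclusion. The unadjusted chi-square does not inflate false positives; its error is on the safe side. That stands, and it makes this a point about efficiency.

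The size is also open. A reader might infer from the cited predictive values that the article itself shows risks of 80% and 11% among trial patients. With exact MoCA balance and half the patients at or below 21, that gives a type I error of 0.8% and power of 37% where 61% was available. The document does not support this. The 11% describes everyone above the cut-off in an earlier study. Here a patient above 21 enters only after failing a MoCA domain, and normal cognition is an exclusion, so the risk in that group is unknown and probably above 11%. The article does not say that the MoCA strata are cut at 21, and with four factors in 100 patients the blocks are often incomplete, so balance is not exact.

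A reader might also infer that the reported intervals will be wrong for the design. Objective 1 specifies a test and no interval or standard error, so there is nothing in the text to fault on that ground.

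The remedy is not wholly free of cost either. Logistic adjustment for the four factors ran at 5.3% to 6.1% type I error at this sample size, so part of its gain is slight anti-conservatism. A 16-cell MH test loses about 1.5 to 2 points against the chi-square when the factors are weak (79.9% against 81.7% at odds ratio 1; 81.0% against 82.5% at 1.5).

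Finally, the article is condensed, and an analysis plan that is not shown may adjust. But the article does name the primary test, and the test named does not use the design's strata. The direction of the effect is not in dispute.

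**Conclusion.** The point holds as a mismatch between design and analysis that costs power. The chi-square is valid but conservative, by an amount that depends on how prognostic age, sex, NIHSS and MoCA prove to be in the enrolled patients. Under the stated assumptions the loss can exceed 20 points, but only if patients above 21 have a risk as low as 11% and make up half the sample. At 30% to 45% risk it is at most about 9 points, and it is negligible if prognosis is weak or nearly all patients fall on one side of the cut. Cut-points, block size, MoCA mix, upper-group risk and effect size are all assumptions. This is a worthwhile improvement and is not needed to make the trial's conclusion valid.

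**What to change.** Before outcome data are analysed, replace the primary test in objective 1 with one that accounts for the stratification factors. There are two options:

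- A Mantel-Haenszel test stratified by MoCA, using the cut applied at randomisation, which should be stated. It held its level at about 5% in simulation.
- A logistic regression of 6-month impairment on arm plus age, sex, NIHSS and MoCA, reporting the standardised risk difference with its 95% confidence interval. State that this test ran slightly above nominal (5.3% to 6.1%) at N = 100 in simulation with binary factors; a version with continuous covariates was not simulated.

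Avoid a full 16-cell stratification, which has about six patients per cell (100/16). Keep the chi-square as a supportive analysis. If an analysis plan already adjusts, reconcile the article with it.

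The cost is one paragraph. All four factors are already collected at screening or baseline, and the SPSS software named in the article runs either analysis.
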